### Data analysis

The normality of the data will be confirmed by a visual inspection of the histograms. A logarithmic transformation [log(x + 1)] for the complete set of data will be used for the variables of asymmetric distribution. In cases where non-parametric distribution persists, all comparisons will be performed with the raw data (without transformation), using the non-parametric tests. The effects of the interventions (between-group differences) will be calculated using linear mixed models by using interaction terms (group allocation versus time), which is equivalent to the between-group differences. The within-group differences will be calculated using repeated measures ANOVA. P-values < 0.05 will be considered as statistically significant. The data will be double checked before analysis. The Statistical Package for the Social Sciences (SPSS) software was used for all analysis.

The clinical relevance of the results will be confirmed by calculating the effect size (Cohen *d*) of the significant differences found between the assessments. The following effects will be considered: 0.00-0.49 small; 0.50-0.79 medium and above 0.80 great (Cohen, 1988).

The calculation of the sample size was performed to detect a difference of 8 points on the Anterior Knee Pain Scale (AKPS) (with a standard deviation estimated at 7.5 points). The alpha level was 0.05 and the statistical power was 80%. Therefore, the sample size required (per group) was 15. We decided to increase the sample to compensate for the loss of patients or to compensate for abnormally distributed data. Each group was increased to 17 (i.e. total sample size of 34 participants).

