### Primary outcomes

The primary outcome was functional capacity, measured after treatment (4 weeks) using the Anterior Knee Pain Scale – AKPS [30].

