### Secondary outcomes

The secondary outcomes were pain intensity, muscle strength of the hip abductors and lateral rotators, extensors of the knee and three-dimensional kinematics of the trunk, pelvis, hip, knee and ankle during the step down test, measured after treatment (4 weeks). In addition, functional capacity and pain intensity were assessed three and six months after randomization.

The description of each of these measurements is described below.

**Anterior Knee Pain Scale – AKPS**: This is a specific questionnaire for anterior knee pain, composed of 13 items that are separated in categories that involve different levels of knee function. Each item was answered and the total result was added to a global index with a maximum score of 100 points, which represents “no deficit”, and a minimum score of zero, representing “the highest possible deficit” [30,34].

**Numerical Pain Rating Scale - NPRS**: This scale measures pain intensity. The score ranges from 0 to 10 points, with 0 representing a “complete absence of pain” and 10 representing the “worst possible pain” [30]. The patients were asked to classify their pain intensity based on the last seven days and while performing the step down test.

**Manual Dynamometer (Lafayette Instrument Company, Lafayette, IN):** This tool is used to quantify muscle strength during maximum voluntary isometric contraction, with adequate reliability in both inter and intra-assessments [32,33]. The abductors, lateral rotators and extensors of the hip and the knee extensors were assessed as described by Bolgla et al. (2011).

**Kinematic Analysis of the Step Down Test:** The Vicon-Nexus® system was used, which involves 8 infrared cameras capable of 250 frames per second (fps) and a resolution of 1MP 1024×1024. This system captured the movements of the reflective markers that were placed on specific anatomical points of the patient’s skin, based on the Vicon® Plug in Gait model [35,36]. All of the cameras were connected to a computer dedicated to treatment of the video signal, which had different functions: timing circuit/control; coordinate generating circuit and interface circuit of the cameras. Once stored in the video memory, the data were transferred to a second general purpose computer. Vicon-Nexus® software was used to process and reconstruct 3D images of the markers through a biomechanical model and a number of mathematical algorithms.

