Static calibration of the system was performed to determine the laboratory reference coordinates (X, Y and Z). Subsequently, dynamic calibration was carried out scanning the volume of interest with a metal rod in the shape of a “T” containing five markers. All of the participants wore shorts to enable the placement and reading of the markers. Their skin was cleaned with cotton and 70% alcohol to improve the fixation of the markers. Twenty-one retro-reflective double-sided spherical markers (14 mm diameter) were fixed (3 M®) to specific anatomical points, which served as a reference for the motion analysis capture system.

The markers were placed in the following locations: on the spinous process of the 7th cervical vertebra; on the spinous process of the 7th thoracic vertebra; on the jugular notch; xiphoid process; anywhere over the right scapula; on the left and right acromioclavicular joint; two anterior and posterior superior iliac spines; in the lateral femoral epicondyles; on the lateral aspect of the thighs; on the lateral malleolus; over the second metatarsals and on the calcaneus. This set of markers was placed following the conventional gait model [35,36].

This set of markers was based on the Helen Hays model that was used to estimate the position of the articular centers, as well as to calculate the three-dimensional kinematics of the pelvis, hip, knee and ankle joints [35,36]. The same experienced examiner positioned the markers in all conditions.

After the capture of the coordinates of the markers, they were named and saved in C3D format. In order to reconstruct the three-dimensional biomechanical model, the coordinates of the markers fixed to the trunk, pelvis, thigh, leg and foot were imported and processed in Vicon Nexus® software. The kinematic data were filtered using a fourth-order zero-lag Butterworth 8-Hz low-pass filter. Joint kinematics were calculated using a joint coordinate system approach [35,36] and were reported relative to a static standing trial in order to quantify the movement of one segment in relation to another or of one segment relative to the laboratory.

The step down test was selected for the three-dimensional analysis. This functional test has often been described in the literature as an assessment method for the quality of lower limb movements [37-40].

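### The log(x + 1) rule ignores skew direction and sign: it worsens a left-skewed AKPS, cannot be computed for angles at or below -1 degree, and should be limited to non-negative, right-skewed variables

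*Protocol article*

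**What the plan says.** All of this is in the protocol article.

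- **Trigger** (Data analysis): "The normality of the data will be confirmed by a visual inspection of the histograms". The direction of skew plays no part.
- **Transformation** (Data analysis): "A logarithmic transformation [log(x + 1)] for the complete set of data will be used for the variables of asymmetric distribution". One formula serves every variable judged asymmetric.
- **Fallback** (Data analysis): "In cases where non-parametric distribution persists, all comparisons will be performed with the raw data (without transformation), using the non-parametric tests". The tests are not named.
- **Planned effect** (Data analysis): the group-by-time interaction of a linear mixed model. The sample size is built on 8 AKPS points with SD 7.5.
- **Primary outcome** (Primary outcomes): "The primary outcome was functional capacity, measured after treatment (4 weeks) using the Anterior Knee Pain Scale – AKPS [30". The scale is a "global index with a maximum score of 100 points, which represents “no deficit" (Secondary outcomes), so the good end is the upper bound.
- **Pain** (Secondary outcomes): "The score ranges from 0 to 10 points, with 0 representing a “complete absence of pain". Here the good end is the lower bound.
- **Kinematics** (Secondary outcomes): joint angles "were reported relative to a static standing trial in order to quantify the movement of one segment" against another, so negative values can arise.

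**The concern.** The function log(x + 1) is concave. It pulls in a long right tail and stretches a long left one, and it exists only for x above -1. It is therefore a remedy for right-skewed, non-negative data, whereas the plan prescribes it for any asymmetric variable.

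Two of the four outcome types fit badly. AKPS is bounded above at its best score, so if patients cluster at the good end after four weeks of active treatment in both arms, the skew is to the left. Joint angles can be negative.

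For AKPS, what is at stake is the effect measure. The trial was sized to detect a difference in points, and an asymmetric primary outcome would be moved away from that scale. For angles, values at one end of the outcome could be lost.

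**Working it through.** **1. The plan's own figure.** With difference 8, SD 7.5, alpha 0.05 (taken as two-sided) and power 80%, the normal approximation gives n = 2 × (1.960 + 0.842)² × 7.5² / 8² = 13.8, so 14 per group. The t-test version gives 14.82, so 15. The stated 15 per group reproduces, and nothing below changes it.

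**2. Left-skewed AKPS.** The document gives SD 7.5 but no AKPS mean or shape, so the means and shapes here are assumptions. Simulated skewness with SD 7.5:

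| Shape | Mean | Raw | After log(x + 1) |
|---|---|---|---|
| Beta on 0–100 | 80 | -0.54 | -0.85 |
| Beta on 0–100 | 85 | -0.79 | -1.11 |
| Beta on 0–100 | 90 | -1.26 | -1.63 |
| 100 minus gamma | 85 | -1.00 | -1.44 |
| Normal censored at 100 | 90 | -0.38 | -0.57 |

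The size depends on the assumed shape. The direction does not, because it follows from concavity.

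**3. What that does to the AKPS test.** T-tests, beta scores, 17 per group:

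| Setting | Raw | log(x + 1) | Mann-Whitney, raw |
|---|---|---|---|
| Type I error, mean 85 | 4.9% | 4.8% | 4.9% |
| Type I error, mean 90 | 4.7% | 4.5% | 4.6% |
| Power for 8 points, control mean 80 | 84.4% | 82.0% | 87.0% |
| Power for 8 points, control mean 85 | 83.6% | 80.3% | 92.5% |
| Power for 8 points, control mean 88 | 82.6% | 77.9% | 97.6% |

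Validity holds on the log scale, and 2.4 to 4.7 points of power are lost.

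**4. What it does to the AKPS effect measure.** On the log scale 8 points is no longer one quantity: 72 to 80 is log(81/73) = 0.104, while 92 to 100 is log(101/93) = 0.083. A log-scale interaction therefore cannot be read against 8 points. In the other branch, the unnamed non-parametric tests are not said to estimate a group-by-time difference.

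**5. Angles.** For x below -1 the function is undefined, and at x = -1 it is minus infinity. Values between -1 and 0 can be computed.

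The document gives no angle values, so take an assumed right-skewed angle: a gamma variable with shape 4 and scale 2 (SD 4, skewness 1), shifted to the required mean.

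- Mean 5 (shift -3): P(x ≤ -1) = P(gamma ≤ 2) = 1 − e⁻¹(1 + 1 + 1/2 + 1/6) = 1.9%.
- Mean 1 (shift -7): P(x ≤ -1) = P(gamma ≤ 6) = 1 − e⁻³(1 + 3 + 4.5 + 4.5) = 35.3%.

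If these values became missing, the remaining means would be 5.1 and 3.1 degrees. A true difference of 4.0 would appear as 2.0. In simulation with 17 per group, t-test power falls from about 80% on raw data to about 35% after logging and deletion.

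The direction matters. The Intervention/control section says the experimental group is trained to correct hip adduction and pelvic drop. If those faults are scored as positive, success moves values towards zero and below, so the better arm would lose more.

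**6. Where the rule works.** For simulated NPRS scores, log(x + 1) reduces skewness from 1.91 to 0.47 at mean 1.5 and from 1.23 to -0.16 at mean 2.5. Muscle force is positive, so the log is always defined for it.

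**The case against.** The strongest reply is the fallback. If the log leaves a variable non-normal, the plan returns to raw data and non-parametric tests. A log that worsens AKPS skew should lead there, and in the simulation the rank test on raw scores kept type I error near 5% with more power than the t-test. The rule also suits two of the four outcomes. NPRS is a likely trigger, and adding 1 is what lets zeros be logged.

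In addition, an AKPS ceiling is not shown. With moderate skew and 17 per group, a histogram might not trigger the rule at all.

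On kinematics, the outcomes are secondary, the text does not say that uncomputable values are dropped, and an analyst could use the raw-data branch. Some angles lie far from -1, since the step-down test is set to 60 degrees of knee flexion. Loss rates computed from a symmetric angle distribution would not count, because a symmetric variable does not trigger the rule.

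All of this stands, and it rules out a stronger reading: a reader might infer that the rule gives wrong results wherever it is likely to be used, or that it invalidates the primary test. The document does not support that.

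The fallback still does not restore the planned estimate. For a left-skewed AKPS both branches leave the point scale, and the choice between them rests on looking at histograms of the collected data. Nor is this detail left to an unseen analysis plan, since the article states the rule and its scope outright.

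**Conclusion.** The concern holds at moderate severity. As written, the rule covers variables for which the transformation cannot do its job.

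- **AKPS:** if it is left-skewed, the log increases the skew, and the primary result loses the group-by-time difference in points. The cost to the test is small (type I error near 5%, about 2 to 5 points of power under the assumed means). The main harm is a result that cannot be set against the 8-point target. This rests on a ceiling that is plausible but undocumented.
- **Joint angles:** values at or below -1 degree cannot be transformed. Outcome-dependent loss follows only if an asymmetric angle is logged and those values are treated as missing. The 2% and 35% rest on an assumed distribution and show what could happen; they are not a forecast.
- **Unaffected:** NPRS when right-skewed, muscle force, and the sample size.

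**What to change.** Limit log(x + 1) to non-negative, right-skewed variables: muscle force, and NPRS if it proves right-skewed. Keep AKPS and all joint angles on their original scale in the linear mixed model. If the residuals are clearly non-normal, keep the model and add a bootstrap or permutation confidence interval for the difference in points or degrees. Other robust methods would also serve, provided that the effect stays in points or degrees and no value is lost because it cannot be logged.

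The cost is one sentence of wording and possibly a small extra analysis. It needs no further patients and no new data.

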### Outcome measures

Four outcome measures were used before and after the interventions: a) Anterior knee pain intensity during activities of daily living was measured by the Anterior Knee Pain Scale – AKPS [30]; b) Pain Intensity was measured by the Numerical Pain Rating Scale - NPRS [30]; c) Maximum isometric muscle force of the knee and hip muscles was measured by the manual dynamometer (Lafayette Instrument Company, Lafayette, IN); d) Kinematic assessment of the trunk and lower limbs during the step down test was performed by the Vicon® movement analysis system.

The above-mentioned scales, which have been translated to Portuguese and cross-culturally adapted for the Brazilian population, are often used to measure pain and functionality in PFPS patients [14,30,31]. The dynamometer is a reliable tool both for inter and intra-assessments of the strength of the knee and hip muscles in women [32,33]. Kinematic analysis is a reliable and commonly used assessment method to quantify lower limb movements [11].

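### The group-by-time interaction is a difference in change from baseline, not the equivalent of the between-group difference; adjusting for baseline AKPS would estimate the same effect more precisely from data already collected

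*Protocol article*

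**What the plan says.** The Data analysis section of the protocol article says that between-group effects will come from "linear mixed models by using interaction terms (group allocation versus time), which is equivalent to the between-group differences". The same section sizes the trial "to detect a difference of 8 points on the Anterior Knee Pain Scale (AKPS) (with a standard deviation estimated at 7.5 points"), at alpha 0.05 and 80% power. This gives 15 per group, raised to 17 to allow for losses or non-normal data. It does not say whether 7.5 is the SD of a score or of a change, and it gives no correlation between visits.

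The outcome hierarchy is clear. Under Primary outcomes: "The primary outcome was functional capacity, measured after treatment (4 weeks) using the Anterior Knee Pain Scale". Under Outcome measures: "Four outcome measures were used before and after the interventions", so a baseline AKPS exists for every participant. Under Secondary outcomes, "functional capacity and pain intensity were assessed three and six months after randomization". AKPS therefore has four time points, of which 4 weeks is primary and 3 and 6 months are secondary.

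**The concern.** A group-by-time interaction compares the arms on how far they have moved from a reference visit. A between-group difference at 4 weeks compares them on where they stand. Randomisation gives the two the same expectation, but they are different estimators with different variances, and in any one sample they give different numbers. Calling them equivalent hides a choice that matters in a trial of 34.

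Two things are at stake. First, a sample size worked out for one contrast need not deliver the same power for the other. Second, an unconstrained difference in change subtracts the whole chance baseline difference, whereas adjustment subtracts only the part that baseline predicts. The same baseline data can therefore give a more precise answer at no extra burden to participants.

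**Working it through.** **Inputs from the Data analysis section:** difference 8 points, SD 7.5, alpha 0.05, power 80%, 15 per group needed, 17 per group randomised. **Assumptions:** two-sided test, equal SDs at baseline and 4 weeks, and a correlation r between them, shown over a range because the article gives none.

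**1. The plan's own figure.** For a two-sample t test, d = 8/7.5 = 1.067. Noncentral-t power is 77.5% at 14 per group, 80.5% at 15 and 85.4% at 17. The stated 15 is reproduced by the plain two-group formula.

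**2. Variances.** Let σ be the SD of a single score. The effective SD per participant is:
- 4-week score alone: σ
- change from baseline (the unconstrained group-by-4-week term): σ√(2(1-r))
- 4-week score adjusted for baseline: σ√(1-r²)

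The variance ratio of change to score is 2(1-r), which equals 1 only at r = 0.5. The ratio of adjusted to change is (1-r²)/(2(1-r)) = (1+r)/2, which is below 1 for every r below 1: 0.65 at r = 0.3, 0.75 at 0.5 and 0.85 at 0.7.

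**3. Power if 7.5 is the SD of a score** (noncentral t; one degree of freedom given up for the covariate):

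| r | SD of change | Change, 15 per arm | Change, 17 per arm | Adjusted SD | Adjusted, 15 per arm |
|---|---|---|---|---|---|
| 0.3 | 8.87 | 66% | 72% | 7.15 | 84% |
| 0.5 | 7.50 | 81% | 85% | 6.50 | 90% |
| 0.7 | 5.81 | 95% | 97% | 5.36 | 98% |

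The change contrast falls below 80% only when r is under about 0.49 with 15 per arm, or about 0.42 with 17. The adjusted contrast stays at 80% or more from r = 0 upwards, at 15 as well as at 17 per arm.

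**4. Power if 7.5 is already the SD of change.** The planned contrast has 80.5% at 15 per arm and 85.4% at 17. Adjustment reduces the effective SD to 7.5√((1+r)/2), that is 6.05, 6.50 and 6.91 at r = 0.3, 0.5 and 0.7. Power at 15 per arm is then 94%, 90% and 86%.

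**The case against.** **The difference in change is a valid estimate.** This stands. Under randomisation the expected baseline difference is zero, so the interaction term and the 4-week difference target the same effect. The equivalence phrase is right in expectation and wrong about the estimate and its variance. The planned analysis is less efficient than it could be, but it is not biased.

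**No loss of power is demonstrated.** This also stands. A reader might infer from the first row of the table that the trial misses its 80%. That needs 7.5 to be the SD of scores and r to be low, and the article supports neither. With r at 0.5 or above, or with 7.5 as the SD of change, the stated power is met.

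**A joint test over all visits is not planned in the text.** A reader might take the interaction to be one test with 3 degrees of freedom across four visits, which could be significant because of months 3 and 6 alone. The article never mentions such a test. It speaks of interaction terms in the plural, makes 4 weeks primary and makes the later visits secondary. With time as a categorical factor, the group-by-4-week term is the 4-week contrast.

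**Model detail belongs in the full protocol or SAP.** This stands in part. Time coding and the handling of baseline may be set out there, and their absence from an article is no fault. The equivalence claim, however, is stated in the article, and a better method can be recommended whatever the unseen document says.

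**Conclusion.** The point holds as a correction of wording and a free gain in precision. The group-by-4-week term in an unconstrained model is a difference in change, and it is equivalent to the between-group difference in expectation only. With equal SDs at the two visits, baseline adjustment needs (1+r)/2 of its variance, a saving of 35%, 25% and 15% at r = 0.3, 0.5 and 0.7.

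What this is worth in power depends on which SD 7.5 is. If it is the SD of scores, adjustment raises power at 15 per arm by about 18, 10 and 2 percentage points at those three correlations. At the lowest of them it lifts the contrast from below 80% to above it. If it is the SD of change, the planned power is already met and adjustment adds about 13, 10 and 6 points. All of this rests on assumed correlations and on reading the model as unconstrained at baseline, which is the usual form but is not spelled out. The sample size of 15, raised to 17, is not shown to be wrong.

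**What to change.** Keep the linear mixed model and make these changes:

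- Treat time as categorical. Either give both arms a common baseline mean (no group term at baseline), or enter baseline AKPS as a covariate with 4 weeks, 3 months and 6 months as the outcome rows.
- Take the group contrast at 4 weeks as the primary test and the 3- and 6-month contrasts as secondary, in line with the outcome sections.
- Delete the phrase that calls the interaction equivalent to the between-group differences.
- State whether 7.5 is the SD of scores or of change.

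The cost is wording and model syntax, plus a documented amendment. The article describes the trial as in progress, with data collection expected to end by July 2014, so the amendment should be dated before anyone sees unblinded data. No extra participants, visits or measurements are needed.

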**Design:**

This is a protocol of randomized controlled trial with a blind assessor. Thirty-four women with a clinical diagnosis of PFPS participated. These participants were allocated into two groups (experimental and control). The experimental group performed twelve sessions to strengthen the knee extensors, hip abductor and lateral rotator muscles in association with neuromuscular training of the trunk and lower extremities. The control group performed the same number of sessions to strengthen the muscles of the hip and knee. The primary outcome was functional capacity (Anterior Knee Pain Scale – AKPS) at 4 weeks. Pain intensity, muscle strength and kinematic changes were also measured during the step down test after four weeks of intervention. Follow up assessments were conducted after three and six months to assess functional capacity and pain. The effects of the treatment (i.e. between-group differences) were calculated using mixed linear models.

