It is known that patients with PFPS exhibit abnormalities in the mechanics and dynamic control of lower limbs. However, very few studies have used neuromuscular training as a treatment strategy and there is insufficient evidence about the influence of this intervention in terms of the clinical and biomechanical aspects of these patients.

The aim of the present study was to compare the effects of a program of neuromuscular training of the trunk and lower limbs, associated with strength training of the hip and knee muscles of women with PFPS, with a program that only involved strengthening of these same muscles in relation to functional capacity. Our hypothesis is that the group submitted to the program that associated strength and neuromuscular training would exhibit better results than the group that only received the strength training.

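### Within-arm change is to come from a separate repeated measures ANOVA, so for AKPS and pain it may rest on fewer patients than the mixed-model treatment effect and not subtract to it (minor)

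*Protocol article*

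**What the plan says.** All of the following is in the Data analysis section of the protocol article unless another place is named.

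- Between-group effects: "The effects of the interventions (between-group differences) will be calculated using linear mixed models by using interaction terms (group allocation versus time"). The abstract agrees: "The effects of the treatment (i.e. between-group differences) were calculated using mixed linear models".
- Within-group change: "The within-group differences will be calculated using repeated measures ANOVA".
- Threshold: "P-values < 0.05 will be considered as statistically significant", with no distinction between the two kinds of analysis.
- Software: "The Statistical Package for the Social Sciences (SPSS) software was used for all analysis".
- Clinical relevance is to be confirmed by "calculating the effect size (Cohen *d*) of the significant differences found between the assessments".
- Losses are expected: "We decided to increase the sample to compensate for the loss of patients". The required 15 per group was raised to 17, and no loss rate is given.

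Under Study design and Secondary outcomes, AKPS and pain have four assessments (baseline, 4 weeks, 3 months, 6 months). Strength and kinematics have two (baseline and 4 weeks). The hypothesis at the end of the Background is between groups: the combined programme "would exhibit better results than the group that only received the strength training".

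**The concern.** Two methods are fixed for the same outcomes, and they usually treat an incomplete record differently. A mixed model uses every visit a patient attends. The usual SPSS repeated measures ANOVA drops a patient who lacks any visit in the model. A woman seen at week 4 but lost at month 6 would count towards the week-4 treatment effect, yet drop out of her arm's week-4 change if the ANOVA covers all four visits. A results table could then show two within-arm changes whose difference is not the treatment effect printed beside them.

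The second issue is how the within-arm P-values are used. They fall under the general 0.05 rule, and the effect-size sentence speaks of significant differences between assessments, which most naturally means time points. On that reading, a significant change within one arm leads to a Cohen d said to confirm clinical relevance. Both arms receive active exercise and neither is untreated, so change within an arm mixes treatment effect, natural course and regression to the mean. It cannot answer a between-group hypothesis.

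**Working it through.** **1. The plan's own figure.** Inputs from Data analysis: difference 8, SD 7.5, alpha 0.05 (taken as two-sided), power 80%. The normal approximation gives n = 2 × [7.5 × (1.960 + 0.842) / 8]² = 13.8, so 14 per group. With the noncentral t distribution, 14 per group gives 77.5% power and 15 gives 80.5%. The stated 15 is reproduced, and 17 per group gives 85.4%. The sample size is not in dispute. The increase from 15 to 17 would cover a loss of 2/17 = 11.8%.

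**2. Patients left in a four-visit complete-case ANOVA.** With three post-baseline visits, an assumed miss rate m at each and misses independent across visits, the share with every visit is (1 − m)³.

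| Assumed m per visit | (1 − m)³ | Of 17 per arm |
|---|---|---|
| 3% | 0.913 | 15.5 |
| 5% | 0.857 | 14.6 |
| 10% | 0.729 | 12.4 |
| 15% | 0.614 | 10.4 |

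Independence is unfavourable to the plan. If the same patients are lost throughout, 10% loss leaves 17 × 0.90 = 15.3. As a yardstick only, since the 15 was set for the between-group test, the count falls below 15 from 5% per visit under independence, but not at 10% if the same patients are lost.

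**3. When the results disagree.** With complete data and no covariate adjustment, the difference between the two arms' mean changes equals the group-by-time contrast, so nothing is inconsistent. Once visits are missed, the two methods can use different patients and the equality can fail.

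**4. Which outcomes.** Four-visit deletion and the sphericity assumption concern AKPS and pain only. With two assessments, as for strength and kinematics, sphericity is not an issue and the ANOVA reduces to a paired comparison.

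**5. How often exactly one arm is significant when both improve equally.** If each within-arm test has power p, the chance is 2p(1 − p). The documents give no within-arm power, so p is computed from a two-sided paired t-test with 17 patients (a two-visit stand-in for the ANOVA) over a range of assumed standardised changes.

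| Standardised change | p | Exactly one arm | Experimental arm only |
|---|---|---|---|
| 0.3 | 0.214 | 34% | 17% |
| 0.5 | 0.491 | 50% | 25% |
| 0.7 | 0.773 | 35% | 18% |
| 0.8 | 0.872 | 22% | 11% |
| 1.0 | 0.972 | 5.5% | 2.8% |
| 1.5 | about 1 | under 0.1% | under 0.1% |

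Discordance is common for moderate changes and rare for large ones.

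**The case against.** The strongest reply is that the text already puts the treatment effect in the right place. The abstract, the hypothesis and Data analysis all define it between groups, from the mixed model. A reader might infer that superiority will be claimed when the experimental arm is significant and the control arm is not; no sentence says so. That reply stands. The effect-size sentence gives within-arm significance some possible interpretive weight, but it concerns labels of clinical relevance and not superiority.

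A reader might also infer that the trial plans to drop every patient with a missed visit. The article does not say how missing visits enter the ANOVA. Dropping them is how the usual SPSS procedure behaves, and handling rules may stand in an analysis plan that is not shown. An ANOVA limited to baseline and week 4 would also lose fewer patients than step 2 shows. This stands as a limit on certainty, but the choice of a second method is fixed in the article and can be judged as written.

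Nor does complete-case analysis bias the changes by itself; that needs missingness related to outcome. Finally, the figures in steps 2 and 5 rest on assumed inputs. Independent misses of 10% and 15% imply 27% and 39% of patients incomplete, well above the roughly 12% that the increase to 17 would cover. All of this lowers the weight of the point. None of it gives a reason to prefer a separate ANOVA.

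**Conclusion.** The point holds as a minor one about secondary results. For AKPS and pain, the within-arm changes may come from fewer patients than the treatment effect and may not subtract to it, provided that visits are missed and the usual SPSS procedure is run over all four visits. Depending on the assumed pattern of misses, roughly 10 to 16 of 17 patients per arm would remain. The primary comparison of AKPS at 4 weeks is unaffected because it comes from the mixed model.

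The effect-size rule is loosely worded and can be read as letting significance within one arm support clinical relevance. How often that would mislead depends on the true change, which the documents do not give: from about 50% of trials with discordant arms at a standardised change of 0.5 to 5.5% at 1.0, with half of these favouring the experimental arm. The documents do not support the stronger reading that superiority is to be judged from within-arm tests.

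**What to change.** In Data analysis, replace the repeated measures ANOVA sentence by one stating that each arm's change from baseline is estimated as a contrast of the same linear mixed model and reported descriptively with a 95% confidence interval. In the next paragraph, tie the effect size and the statement on clinical relevance to the between-group contrast, so that differences between assessments within an arm no longer trigger it. The cost is two sentences of wording: the model is already being fitted, and no extra patients, visits or data are needed. The sample size is unchanged.
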